### Procedure

Additional file 1: Figure S1 summarises the study design. Screening will occur in three stages and will be staggered to accommodate limited resources and staffing.

#### Screening stage 1

Potential participants will be initially screened by telephone via the Computer Assisted Telephone Interview system, which is an efficient method of recruitment used for a previous study [13]. During the initial contact, the purpose of the study will be explained and the caller will determine whether the individual meets the initial screening criteria. This will incorporate a number of diabetes risk factors based on AUSDRISK, an Australian type 2 diabetes mellitus risk assessment tool utilising anthropometric, lifestyle, and demographic measures [14]. This simple and reliable questionnaire will screen those at high risk of developing type 2 diabetes mellitus (risk score ≥12). Findings from our pilot data indicate that in order to achieve the required sample size, 1000 people with high risk scores will require to be screened for potential inclusion into the study.

#### Screening stage 2

After stage 1, participants meeting the initial selection criteria and indicating an interest in the study will be sent information explaining the home-based intervention project, their rights, and confidentiality details. An appointment will then be made for them to attend a central location in Albany for anthropometric measurements, blood pressure readings, and completion of a questionnaire.

#### Screening stage 3

Participants with confirmed central obesity based on screening stage 2 results will then be asked to attend a blood collection centre in Albany for the collection of a fasting blood sample (triglycerides, glucose, cholesterol) to determine whether they are at risk of metabolic syndrome.

Once eligibility criteria are determined, random assignment to intervention and control groups will occur, with quota sampling for gender. Suburbs and postcodes will be ranked according to the Socio-Economic Index for Areas and equal numbers of low and high scoring suburbs and postcodes will be allocated to each group. Intervention participants will be briefed about the purpose of the control group and the importance of refraining from communication about the program with control group members during the intervention period. They will receive the intervention materials and their AUSDRISK scores to emphasise the relevance of the program and the need for compliance to the lifestyle intervention.

### Intervention

As part of this 6-month home-based intervention, each participant will be provided with a package designed to educate, motivate, and support improvement in nutrition and levels of physical activity through goal setting, based on the principles of Self-Determination Theory and Motivational Interviewing [15,16]. The program will empower individuals to self-manage and monitor their health behaviours and weight within their own environment (home). The approach will take particular care to emphasise the importance of regular self-weighing which is widely associated with greater weight loss (showing a 1 to 3 BMI unit advantage over individuals who do not self- weight frequently) [17]. In addition, frequent self-weighing is an important behavioural mediator in weight loss maintenance [18].

The intervention program is based on recent successful physical activity and nutrition programs (Physical Activity & Nutrition for Seniors [PANS] and the Perth Active Living Seniors [PALS]) specifically designed for older adults by the research team [19,20]. It will be adapted for the younger age group and the rural context. The intervention is safe, accessible, and low cost. Participants will commence it at a low level of physical activity, with aerobic, strength and flexibility components commensurate to the fitness level of each individual. The educational materials will provide illustrations and tips on how to perform exercises safely. The physical activity component will use accelerometers to measure programmed and incidental physical activity at baseline and post-test for the intervention group only, with graphical feedback provided to participants at baseline. The nutrition component will consist of suggested meal plans, recipes, and tips on healthy eating, encouraging a higher consumption of fruit/vegetables and fibre while reducing intake of saturated fat and sugar.

Research assistants will assist with the delivery of intervention resources and liaise with the participants to provide support and to monitor their goal setting. These assistants will receive a training manual including guidelines for diet and physical activity adherence, and will undergo training in Motivational Interviewing techniques [21]. They will make telephone contact with participants at weeks 3, 6, 12, 18 and 24 of the intervention. Additionally, follow-up emails will be used, and participants will have the option to contact the research assistant they have been allocated to.

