### Recruitment

Study participants aged 50–69 years and insufficiently active (less than 150 minutes of moderate physical activity per week) [11] will be recruited. Additional criteria for metabolic syndrome is based on assessing the following International Diabetes Federation (IDF) metabolic syndrome criteria [5]: central obesity (waist circumference >94 cm men or >80 cm women [Europids, Sub-Saharan Africans, Eastern Mediterranean, Middle East]; >90 cm men or >80 cm women [South Asians, Chinese, Japanese]); plus any two of: raised triglyceride level (>1.7 mM, or treatment for this); reduced HDL-cholesterol (<1.03 mM in males and <1.29 mM in females, or treatment for this); raised blood pressure (systolic ≥130 mmHg or diastolic ≥85 mmHg, or treatment of previously diagnosed hypertension); raised fasting plasma glucose (≥5.6 mM). However, only one instead of two of the latter four conditions needs to be satisfied to increase the potential pool of at risk participants. Identifying participants at risk of developing metabolic syndrome will enable appropriate intervention to be implemented, with the aim of preventing the onset of the syndrome and potential for type 2 diabetes and cardiovascular disease [12].

The following exclusion criteria will apply: previous diagnosis of diabetes mellitus (other than gestational diabetes); receiving treatment to lower blood glucose; on a weight loss diet or having weight fluctuations of >5% within the past 6 months; involvement in another physical activity and/or nutrition program; or a partner/individual residing in the same household as another participant already recruited for the study (to avoid contamination).

After the initial screening (n = 1000), it is expected that 625 participants will be eligible to join the study. Allowing for a subsequent 5% withdrawal rate and another 15% loss to follow-up, a final sample size of n = 250 intervention and n = 250 controls is anticipated, with quota sampling to ensure equal numbers of males and females. These figures are based on the pilot recruitment and data collection phase of the study.

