### Control group

The control group (n = 250) will be placed on a ‘waitlist’ to receive the intervention after they compete the post-test data collection. This group will not receive their risk scores; however will be informed they are eligible for the study after the first group have completed their program. Previous interventions have adopted this method of wait listing the control group [25,26].

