### Statistical analysis

Comparisons between the changes in intervention and control groups will be performed using univariate and multivariable statistical methods. Outcome variables at baseline and post- intervention will be used to test the hypotheses in association with the covariates and confounding demographic and lifestyle variables. Continuous and categorical outcomes will be analysed using generalised linear mixed regression models, accounting for the correlations between repeated measures and clustering of the observations. Intention-to-treat analysis will be conducted to assess sensitivity of the results to the expected attrition and withdrawal of participants from the RCT.

All qualitative data will be transcribed within two weeks of interviewing. At least 10% of all data will be randomly selected and reviewed. Data will be coded and common themes or categories created. The information obtained will be collated, presented thematically and supported by direct quotes from participants. Data management of full transcripts and other text will be facilitated by NVIVO [38]. Participants’ permission will be obtained but they will not be identified in transcripts.

The economic analysis will involve both a cost analysis and cost-effectiveness analysis. This will be carried out from the perspective of the health services, including both Medicare and non- Medicare health costs, over a time horizon of 2 years. A cost analysis will provide information relating to set up, recruitment and program implementation of the RCT. While the analysis will provide specific cost details about running the RCT, the main interest will focus on the costs associated with future roll-out. Estimation will allow healthcare organisations to gauge the cost of conducting a similar program in the future.

The cost-effectiveness analysis of the trial intervention will involve the construction of a decision analytical model that captures data on both the cost and effectiveness of the intervention and non- intervention groups. The cost-effectiveness analysis will compare the difference in costs and effectiveness of the intervention and control groups, by calculating the incremental cost per Quality-Adjusted Life-Years gained by the intervention.

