### Sample size

The power calculations are based on a logistic mixed regression model with the outcome variable being the prevalence of physical activity participation. Assuming 80% complete data across the assessments due to attrition and non-respondents, a total of n = 625 subjects satisfying the selection criteria will be initially recruited. In the power analyses, effect sizes of interest are associated with the time (pre-post) and intervention group parameters. For the mixed regression analysis, a final sample size of n = 500 [125 per gender by intervention condition] will provide sufficient power (80%) to detect a medium effect size at 5% significance level for the group by time interaction term accounting for gender but without other covariate adjustment.

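### Support by allocated research assistants may cluster outcomes in the intervention arm only; the analysis section names no cluster unit and the stated 80% power shows no allowance for it

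*Protocol article*

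**What the plan says.** All references are to the protocol article.

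- **Intervention.** Research assistants, trained in Motivational Interviewing, help deliver the resources and "liaise with the participants to provide support and to monitor their goal setting". "They will make telephone contact with participants at weeks 3, 6, 12, 18 and 24 of the intervention". In addition, "participants will have the option to contact the research assistant they have been allocated to". Neither the number of assistants nor their caseload is given.
- **Control group.** Controls are wait-listed "to receive the intervention after they compete the post-test data collection". No support contact is described for them before then. Research assistants do take blood pressure (Outcome measures), but that is a measuring role, not a supporting one.
- **Statistical analysis.** Generalised linear mixed models are planned, "accounting for the correlations between repeated measures and clustering of the observations". The cluster unit is not named.
- **Sample size.** Power comes from a "logistic mixed regression model with the outcome variable being the prevalence of physical activity participation". It is given as 80% at the 5% level for a medium effect with 500 completers, "for the group by time interaction term accounting for gender but without other covariate adjustment". Recruitment is raised to 625 for incomplete data. No design effect, ICC or caseload appears.

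**The concern.** People supported by the same assistant may end up more alike than people supported by different ones, because assistants can differ in skill, persistence and style. In this trial that grouping exists in the intervention arm and not among controls. It arises even when individuals are randomised. Excluding a second member of a household (Recruitment) does not remove it.

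Two things are at stake. If the assistant is left out of the model, the standard error of the between-arm difference is too small and the type I error exceeds 5%. If the assistant is modelled, the standard error is right but power falls below what independent data would give. A generic cluster term common to both arms, such as area of residence, would not deal with either, because controls have no assistant to be grouped by.

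The two sections also do not match: the analysis section expects clustering of some kind, while the power statement shows no allowance for any.

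**Working it through.** **1. The plan's own figures.** 500 / 0.80 = 625, which reproduces the recruitment target. Attrition uses up the whole inflation, so nothing is left for clustering. The 80% power cannot be reproduced, because the medium effect, the baseline prevalence and the pre-post correlation are not given in numbers.

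**2. Inputs.**
- From the documents: 250 completers per arm ("a final sample size of n = 250 intervention and n = 250 controls is anticipated"), 5% level, 80% power.
- Assumed: two-sided test; k = 5 or 10 assistants with equal caseloads m = 250/k; ICC 0, 0.01, 0.02 or 0.05 at post-test; pre-post correlation 0.5; 500 giving exactly 80% under independence; a continuous-outcome normal approximation standing in for the binary mixed model.

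**3. Formulas.**
- Design effect in the intervention arm: DE = 1 + (m − 1) × ICC.
- Variance inflation of the between-arm difference, with one arm clustered: VIF = (DE + 1)/2.
- Power when clustering is modelled: Φ((1.96 + 0.84)/√VIF − 1.96).
- Type I error when clustering is ignored: 2 × (1 − Φ(1.96/√VIF)).

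Example, k = 5 and ICC 0.05: m = 50, DE = 1 + 49 × 0.05 = 3.45, VIF = 4.45/2 = 2.225, √VIF = 1.49. Power = Φ(2.80/1.49 − 1.96) = 47%. Type I error = 2 × (1 − Φ(1.96/1.49)) = 19%.

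**4. Results.**

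| Assistants | ICC | DE | VIF | Power, normal | Power, small-sample t | Type I error if ignored |
|---|---|---|---|---|---|---|
| 5 | 0 | 1.00 | 1.00 | 80% | – | 5% |
| 5 | 0.01 | 1.49 | 1.25 | 71% | 63% | 8% |
| 5 | 0.02 | 1.98 | 1.49 | 63% | 54% | 11% |
| 5 | 0.05 | 3.45 | 2.23 | 47% | 36% | 19% |
| 10 | 0 | 1.00 | 1.00 | 80% | – | 5% |
| 10 | 0.01 | 1.24 | 1.12 | 75% | 73% | 6% |
| 10 | 0.02 | 1.48 | 1.24 | 71% | 68% | 8% |
| 10 | 0.05 | 2.20 | 1.60 | 60% | 56% | 12% |

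The small-sample column uses Satterthwaite degrees of freedom, with k − 1 for the assistant component.

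**5. Sensitivity to the pre-post correlation ρ.** If the assistant effect is present at post-test only, the inflation for a change is VIF = 1 + (m − 1) × ICC / (4(1 − ρ)). This equals the formula in step 3 only at ρ = 0.5. For k = 5 and ICC 0.05, (m − 1) × ICC = 2.45:
- ρ = 0: VIF = 1 + 2.45/4 = 1.61, power 60%, type I error 12%.
- ρ = 0.5: VIF = 2.23, power 47%, type I error 19%.
- ρ = 0.7: VIF = 1 + 2.45/1.2 = 3.04, power 36%, type I error 26%.

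**6. Sensitivity to the meaning of medium.** With 250 per arm, exactly 80% power corresponds to d = 2.80 × √(2/250) = 0.25. If medium means d = 0.5, power under independence is 99.99%. With 5 assistants and ICC 0.05, the standard error is √(3.45/250 + 1/250) = 0.133, and power is Φ(0.5/0.133 − 1.96) = 96% (89% with small-sample t). The type I error column does not change, because it does not involve the effect size.

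**The case against.** A reader might infer that the trial assumes 500 independent people and so fails to deliver 80% power. The documents do not support that as a fact.

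- Independence is never stated. It is inferred from the absence of any allowance.
- No ICC is given, and a value near zero is compatible with the text: the programme is home-based and largely self-managed, assistants work from a common manual, and the scheduled calls number five. At ICC 0 nothing is lost.
- It is not stated that the allocated assistant makes all of a participant's calls.
- The power figures are calibrated to exactly 80%. With d = 0.5 there is ample slack for small ICCs.

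A reader might equally infer that type I error will be inflated. That follows only if the planned adjustment for clustering leaves the assistant out, and nothing says that it does. Naming the unit and the random-effects structure is often left to a statistical analysis plan, which is not shown here.

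These points limit the claim but do not remove it. The allocation to assistants in one arm is stated in the article. So are an analysis that expects clustering and a power figure that, as described, allows only for attrition. Taking the stated 80% at face value is a fair starting point for an illustration. The type I error risk holds however medium is read.

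**Conclusion.** The point holds in a conditional form. One-arm grouping by assistant is part of the design, the analysis section does not say that its clustering term covers it, and the power statement shows no allowance for it. The 80% is therefore not assured; it has not been shown to be wrong.

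For 5 to 10 assistants and ICCs from 0 to 0.05, power runs from 80% down to 47% (normal approximation), and lower with small-sample degrees of freedom. Type I error, if the assistant is ignored, runs from 5% to 19%. These ranges rest on the assumed number of assistants, ICC and pre-post correlation of 0.5, and the power range also on 500 giving exactly 80% under independence. If medium means d = 0.5, power is a lesser concern and the validity of the standard errors is the main one. This should be settled before analysis, because it bears on between-arm comparisons generally.

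**What to change.** 1. Record the allocated assistant's ID for every intervention participant.
2. State that the clustering to be modelled includes the assistant. Fit a partially nested mixed model: a random assistant effect for the intervention arm at post-test only, none for controls, with small-sample degrees of freedom. Post-test only is appropriate because the screening measurements and blood samples precede randomisation, and so precede any assistant contact under the programme.
3. Restate the power in the Sample size section with a numeric effect size, as a range over ICCs from 0 upward for the actual number of assistants.

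The cost is one more random term, one ID variable that staff should already hold, and a less favourable stated power. No extra participants are needed. The model protects the standard errors; it does not restore any power lost to clustering.

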### Program resources

#### Booklet

Participants will receive a booklet designed to educate and motivate improvements in nutrition and physical activity. Content will be developed from the PANS materials [13] and adapted for a rural context. Materials will be based on the Australian Dietary Guidelines [22] and Australia’s Physical Activity and Sedentary Behaviour Guidelines [11]. Participants will be required to set their own goals for the duration of the intervention to ensure the program suits their individual needs.

#### Exercise chart, calendar, and resistance bands

The calendar will support participants’ goal setting by providing a resource for their planning, and recording their physical activity and eating habits, and will supplement the program booklet as a quick and convenient reference. Participants in the intervention group will be provided with a resistance band to use for strength training exercises. Instructions and photographs demonstrating safe and correct use will be summarised in an exercise chart [13].

#### Nutrition panel wallet cards

The wallet cards will provide assistance to participants when choosing healthy food options in a supermarket setting. The card will include information usually found on nutrition panels such as saturated fat, sugar, fibre, salt, common names for nutrients, and amounts per serve and per 100 grams considered to be healthy options.

#### Website

An online component will be developed to provide materials in electronic format to the intervention group. Pages will include nutrition and physical activity information and links, a blog for program news and updates, and a daily and weekly progress tracker enabling participants to log and track their physical activity and nutrition behaviours and monitor their weight. The website will be password protected, allowing access by the intervention group only during the study period.

#### Newsletter

A bi-monthly newsletter will be sent to intervention participants via the website, email, and post (for those without internet), to maintain participation. Previous research has shown that a 1–2 page newsletter containing health information is usually positively received in program of this nature [23,24].

### Control group

The control group (n = 250) will be placed on a ‘waitlist’ to receive the intervention after they compete the post-test data collection. This group will not receive their risk scores; however will be informed they are eligible for the study after the first group have completed their program. Previous interventions have adopted this method of wait listing the control group [25,26].

### Outcome measures

Table 1 summarises measurement of each outcome variable.

**Table 1 Tab1:** **Summary of outcome variables**

***Outcome variable***	***Measuring instrument***
Metabolic syndrome diagnosis/status	IDF criteria [5]
Glucose, triglyceride, cholesterol (total, LDL, HDL, non-HDL)	Blood samples [27]
Blood pressure	OMRON automatic BP monitor
Anthropometric measurements (BMI, waist circumference, waist-to-hip ratio, body fat and muscle percentage)	Body composition scale, stadiometer, measuring tape [28,29],
Physical activity (programmed, incidental)	ActiGraph GT3X Accelerometer [30]
Sedentary and physical activity behaviours	IPAQ [13]
Diet (fat, fibre, fruit, vegetable consumption)	Fat & Fibre Barometer [31]
Economic analysis	EQ-5D-3 L [32]

*Metabolic syndrome status* will be determined using the IDF criteria [5]. Participants satisfying the full criteria will be classified as having metabolic syndrome; whereas those with central obesity (waist circumference >94 cm men or >80 cm women [Europids, Sub-Saharan Africans, Eastern Mediterranean, Middle East]; >90 cm men or >80 cm women [South Asians, Chinese, Japanese]) plus any one of: raised triglyceride level (>1.7 mM, or treatment for this); reduced HDL-cholesterol (<1.03 mM in males and <1.29 mM in females, or treatment for this); will be classified as being at risk of metabolic syndrome. Post-test reclassification will determine changes to metabolic syndrome status after 6 months.

*Blood samples* will be taken by a phlebotomist at baseline and 6 months to measure a range of markers of cardiovascular disease risk and metabolic syndrome status. Fasting plasma glucose will be measured to assess insulin sensitivity. Fasting lipid levels will also be determined to assess lipid profile and CVD risk. The concentrations of triglycerides, total cholesterol and HDL cholesterol will be measured allowing determination of total-, LDL-, HDL-, and non-HDL-cholesterol levels [27]. All blood tests will be performed by Western Diagnostic Pathology.

*Anthropometric measurements* will be undertaken by a certified anthropometrist at baseline and at 6-months post-test, following the International Society for the Advancement of Kinanthropometry guidelines. These include height and weight, body fat and muscle percentage, waist and hip circumference using a portable stadiometer, body composition scale, and tape measures, respectively [28,29]. *BMI* is promulgated as the most useful epidemiological measure of obesity along with *waist circumference*, while *waist-to-hip ratio* has been suggested as a better predictor of CVD mortality [33]. *Height* will be measured while the participant is barefoot to the nearest 0.1 cm with a portable stadiometer. *Weight* will be measured (wearing light clothing without shoes) using an electronic scale and recorded to the nearest 0.01 kg. *Waist and hip circumference* will be measured standing up at the level midway between the lowest rib margin and the iliac crest to the nearest 0.5 cm. *Hip* circumference will be measured at the largest level of the symphysis pubis and gluteus maximus. *Waist-to-hip ratio* will be calculated as waist circumference divided by hip circumference. *Blood pressure* will be measured by the trained research assistants using an Omron M5-1 electronic sphygmomanometer. A mean value will be recorded after three consecutive measurements (30).

A *self-reported questionnaire* will be completed by all participants at baseline (0-month) and post- test (6-months). This will include questions on demographics and lifestyle (smoking and alcohol drinking), the *International Physical Activity Questionnaire* (IPAQ) [13], and the *Fat & Fibre Barometer,* a valid and reliable instrument to assess dietary behavioural change [31]. The IPAQ Short Form has undergone reliability and validity testing in 12 countries. It has been used in many settings and was specifically designed for population-based physical activity studies.

*Accelerometers (ActiGraph GTX3)* will be used to objectively measure physical activity in the intervention group [30]. Participants will be asked to wear an accelerometer for 7 days at baseline and at post-test. It will be worn at the left hip throughout waking hours, removed only for showering and swimming. Data collection will be set at one-minute intervals over the day. This information will be downloaded by researchers using the ActiLife 6 software. Data will be summarised into daily average counts (counts/mins/day) and activity durations (mins/day) in specific intensity levels (inactive, light, moderate, and vigorous). A calculated weight bearing Metabolic Equivalent Task score will be determined and compared within and between groups. This will allow monitoring of incidental activity and assessment of the effect of the intervention on physical activity levels. To ensure compliance, participants will receive instructions on the device and also complete a daily log [34].

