## Methods

### Study design

This 6-month RCT will identify and recruit insufficiently active adults aged 50 to 69 with central obesity, residing in Albany, Western Australia, to participate in a home-based physical activity, nutrition, and healthy weight management intervention. Additional file 1: Figure S1 summarises the study design. A total of 500 participants with or at risk of metabolic syndrome will be recruited and randomised into intervention (n = 250) and wait-listed control (n = 250) groups. Data will be collected from both groups at baseline and 6 months to assess changes in outcome measures. Ethical approval of the study has been obtained from the Human Research Ethics Committee of Curtin University (HR149_2013). All participants will be informed of the research aims and objectives, and that confidentiality will be maintained throughout the study. Information and consent forms will be provided prior to entry into the RCT and participants will be free to withdraw from the program at any time.

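### The outcome definition of at-risk status omits blood pressure and glucose, so some eligible participants fall in neither metabolic syndrome class

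*Protocol article*

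**What the plan says.** **Eligibility.** The Recruitment section lists central obesity and four further conditions. Two of these are "raised blood pressure (systolic ≥130 mmHg or diastolic ≥85 mmHg, or treatment of previously diagnosed hypertension") and "raised fasting plasma glucose (≥5.6 mM"); the other two are raised triglycerides and reduced HDL-cholesterol. It then relaxes the usual requirement: "only one instead of two of the latter four conditions needs to be satisfied".

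**Population.** Study design describes everyone enrolled in these terms: "A total of 500 participants with or at risk of metabolic syndrome will be recruited". Under Procedure, screening stage 3 uses a "fasting blood sample (triglycerides, glucose, cholesterol) to determine whether they are at risk of metabolic syndrome", so glucose counts towards at-risk status there.

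**Outcome.** The text below Table 1 says that status follows the IDF criteria and sets out two classes. For the first: "Participants satisfying the full criteria will be classified as having metabolic syndrome". For the second, it repeats the waist cut-offs, lists triglycerides and HDL-cholesterol, and ends: "or treatment for this); will be classified as being at risk of metabolic syndrome". Blood pressure and glucose do not appear in that list. The classes are then used for the trial's comparison over time: "Post-test reclassification will determine changes to metabolic syndrome status after 6 months".

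**The concern.** The entry rule and the outcome rule use the same term, at risk, for different sets of people. A participant who enters on raised blood pressure alone, or on raised fasting glucose alone, is eligible but has neither the syndrome nor at-risk status under the outcome definition. That contradicts the Study design section, where everyone enrolled is one or the other.

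The at-risk class matters here because the entry rule was relaxed precisely to bring in people with a single condition, and preventing the syndrome in them is one of the trial's aims. An analyst who follows the outcome text literally has to invent a treatment for the unclassified participants: leave them out, or call them free of risk. An analyst who silently restores the missing items departs from the published definition.

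**Working it through.** No figure in the article depends on this definition, so there is nothing to reproduce first. The check is an enumeration.

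**Inputs.** Four conditions, each present or absent: triglycerides (TG), HDL, blood pressure (BP) and glucose (GLU). Central obesity is present in every enrolled person. Eligibility requires at least one of the four (Recruitment). Metabolic syndrome requires at least two of the four (the full criteria, as listed in Recruitment). Syndrome takes precedence over at risk.

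**Step 1: eligible patterns.** 2^4 − 1 = 15.

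**Step 2: assign each pattern to a class.**

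| Class | At-risk list as printed (TG, HDL) | At-risk list with all four conditions |
|---|---|---|
| Metabolic syndrome (two or more) | 11 | 11 |
| At risk | 2 (TG only, HDL only) | 4 (TG, HDL, BP or GLU only) |
| No class | 2 (BP only, GLU only) | 0 |
| Total | 15 | 15 |

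The syndrome row is the same in both columns.

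**Step 3: the 6-month reclassification.** Take two participants who both start with BP plus TG (metabolic syndrome), stay centrally obese and each lose one condition.
- BP normalises and TG remains: printed class, at risk.
- TG normalises and BP remains: printed class, none.

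Both went from two conditions to one, but their labels differ. With all four conditions in the list, both would be at risk. Under either definition, both have left the syndrome.

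**Step 4: how many people this could involve.** The article gives no prevalences. Purely as an illustration, assume that the four conditions are independent among centrally obese people, with prevalences of BP 40–70%, GLU 20–30%, TG 30–50% and HDL 20–40%. Then:

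- share unclassified = (1−TG)(1−HDL)[BP(1−GLU) + GLU(1−BP)] / [1 − (1−TG)(1−HDL)(1−BP)(1−GLU)]

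Each prevalence enters as a ratio of linear terms, so the extremes lie at the corners of the ranges.

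- Lowest (BP 0.40, GLU 0.20, TG 0.50, HDL 0.40): numerator 0.30 × (0.32 + 0.12) = 0.132; denominator 1 − 0.30 × 0.60 × 0.80 = 0.856; share 15.4%, or about 77 of 500.
- Highest (BP 0.70, GLU 0.20, TG 0.30, HDL 0.20): numerator 0.56 × (0.56 + 0.06) = 0.3472; denominator 1 − 0.56 × 0.30 × 0.80 = 0.8656; share 40.1%, or about 201 of 500.
- A set inside the ranges (BP 0.60, GLU 0.25, TG 0.35, HDL 0.25): 0.268 / 0.854 = 31%.

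**The case against.** The best reply is that this is a truncated list and not a chosen definition. The outcome text matches the Recruitment list up to the HDL item, then breaks off at a semicolon just before the classification. Recruitment, Study design and screening stage 3 all point to the four-condition meaning, so an analyst reading the whole article would probably apply it. That is a fair account of how the text arose. It does not remove the problem, because nothing in the article corrects the sentence, and it is the only place where the outcome class is defined.

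Two stronger readings are tempting and do not hold.
- A reader might infer that the whole post-test reclassification is wrong, or that recovery from the syndrome is overstated. The article does not support this. Syndrome yes/no rests on the full criteria and is defined for everyone at both visits, and the number leaving the syndrome is the same under either list. Only the label given to people without the syndrome changes.
- A reader might infer bias between the arms. The same wording applies to both groups, and nothing in the article shows a differential effect.

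It also stands that the article does not designate metabolic syndrome status as primary; being listed first in Table 1 does not make it so. The Sample size section bases power on physical activity participation, which this point does not touch.

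**Conclusion.** The point holds in a limited form. The at-risk definition under Outcome measures conflicts with Recruitment, Study design and Procedure. Followed as written, it leaves 2 of the 15 eligible patterns without a class at baseline, and it labels equal improvement unequally at 6 months. This count follows from the definitions and needs no assumption beyond giving syndrome precedence over at risk.

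The effect is confined to the at-risk class and to moves into or out of it. The number of people affected is unknown. The range of about 15 to 40% depends entirely on the assumed prevalences and on independence, and should not be read as an estimate for this trial.

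**What to change.** Reconcile the outcome text with Recruitment so that both use the same four conditions, and define three exclusive and exhaustive classes for use at both visits:
- **Metabolic syndrome:** central obesity plus at least two of the four conditions.
- **At risk:** central obesity plus exactly one of the four.
- **Neither:** everyone else. At 6 months this covers people who are no longer centrally obese and those with none of the four conditions remaining.

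Run the 6-month reclassification on these classes, and settle the wording before outcome data are examined by group. The cost is a short text correction. Bloods are taken at baseline and 6 months, blood pressure and waist circumference are listed outcomes, and Study design has data collected from both groups at both times. No measurement, sample size or eligibility rule has to change.
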